### Data Analysis

To achieve aim 1, composite scores will be calculated for each laser procedure, encompassing the pain score, pain medication use during the procedure, and whether rescue medication was used. The rationale for choosing the composite score as the outcome is that prior researchers have shown a significantly high positive relationship between pain medication use and self-reported pain scores [40]. From a clinical perspective, pain scores alone are influenced by the patients’ actual opioid use and may not fully reflect the treatment benefit of VR [41]. The composite score approach, therefore, provides a single, patient-centered outcome that represents overall analgesic benefit, aligning with the goal of achieving adequate pain control while minimizing opioid exposure. In our analysis, we will apply the rank-based approach by Dai et al [40] to assign weights to pain and medication use, reflecting their complementary clinical importance as measures of pain reduction [41]. In the primary analysis, the composite scores from the laser procedure with VR will be compared to those from the procedure with standard care (ie, control) using paired 1-tailed *t* tests or the Wilcoxon signed rank tests (depending on the distribution of the composite scores) due to the cross-over design. The clinical effect size will be the mean difference (if paired *t* tests are used) or median difference (if Wilcoxon signed rank tests are used) in the composite score between VR and control procedures. The SD of the difference will also be calculated.

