Linear mixed-effects models with participant-specific random intercepts will be fit on the composite scores to evaluate any modification of the effects of VR on pain by sex, age, and anxiety, with adjustment for baseline covariates and potential carryover effects of VR from the first to the second procedure. The following covariates will be included in the regression models: study group (VR vs control), period (second vs first procedure), study group by period interaction (test for carryover effect), age, age by study group interaction, sex, sex by study group interaction, procedural anxiety, procedural anxiety by study group interaction, race, ethnicity, State-Trait Anxiety Inventory for Children, 6-item State-Trait Anxiety Inventory, and average mYPAS scores between T0 and T1. We will include each of the 3 interaction terms in a separate regression model. Due to the limited sample size, testing the interaction may not be feasible. The study will then run the main linear models without interaction terms. The results will provide us with preliminary data to estimate the future study sample size and power. In case a significant carryover effect is detected, we will use only data from the first procedure to evaluate the VR effect using 2-sample *t* test or Wilcoxon rank sum tests (depending on the distribution of the composite scores).

All statistical analyses will follow the intention-to-treat principle, wherein participants will be analyzed according to their assigned study groups, regardless of compliance status or group switching during the study.

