## Results

This study was funded by an intramural grant from the Clinical and Translational Science Institute at NCH (grant: IFPAWRI012023) in January 2023. Enrollment started in January 2023, and data collection was completed in November 2025. The flow of participants can be seen in Figure 1. A total of 44 patients were recruited and completed the first visit, with 40 participants completing both visits. The sample was balanced, with 40 patients using the VR intervention and 40 patients participating in the control group. Reasons for not completing both visits included discontinuing laser treatment (n=3) and a lack of interest in playing the VR game (n=1). Among those who completed both visits, the age range of the sample was 6 to 21 years at recruitment, and 55% (n=22) were female. Data analysis is expected to be finished in June 2026, with a paper to follow. Future results will be disseminated through publications in peer-reviewed journals and abstracts submitted to conferences in relevant disciplines.

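### The primary paired test for aim 1 has no period term and uses complete pairs only, so a shift between visits inflates the SD of the difference and widens the CI

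*Protocol article*

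**What the plan says.** All references are to the protocol article.

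- **Data Analysis, aim 1.** The text reads: "In the primary analysis, the composite scores from the laser procedure with VR will be compared to those from the procedure with standard care". The method is a paired one-tailed t test or "the Wilcoxon signed rank tests (depending on the distribution of the composite scores) due to the cross-over design". The effect size is the raw mean difference or the "median difference (if Wilcoxon signed rank tests are used) in the composite score between VR and control procedures", and the SD of the difference is reported as well. Period does not enter.
- **Data Analysis, mixed models.** Random-intercept models on the same composite score include study group, period and their interaction, with many other covariates. Their stated purpose is to look for effect modification by sex, age and anxiety. If interactions cannot be tested, models without them will be run, and the results are to inform the next trial's size and power.
- **Data Analysis, closing paragraph.** "All statistical analyses will follow the intention-to-treat principle, wherein participants will be analyzed according to their assigned study groups", whatever their compliance or switching. The Abstract ties the principle to the assignment at each visit.
- **Results.** "A total of 44 patients were recruited and completed the first visit, with 40 participants completing both visits". Three of the four others stopped laser treatment, and one was not interested in playing the game.
- **Sample Size.** The 40 rests on budget and patient volume. The stated focus is on effect sizes, their 95% CIs and outcome variances, for planning larger trials.

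**The concern.** In a two-period crossover, each within-person VR-minus-control difference contains the treatment effect plus or minus the period effect, depending on sequence. A paired test that ignores sequence treats this systematic component as noise. Some period effect is plausible on the protocol's own account: patients enter at the first procedure of a new series (Settings and Participants), and the Introduction says that procedural distress can affect later treatments.

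Two things are at stake. The CI for the headline estimate is wider than the design requires. Also, the reported SD of the difference, one of the pilot's main products, absorbs the period shift and would oversize a later crossover trial that does adjust for period. If the completers are also unequal by sequence, the period shift no longer cancels and some bias appears.

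The pairing requirement excludes the four one-visit participants, who were all randomised before their first procedure (Randomization and Blinding). One of them left for a reason connected with the intervention.

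**Working it through.** **No figure to reproduce.** The sample of 40 has no power basis, and the article gives no SD, within-person correlation or period effect. The illustrations below are therefore on the NRS 0-10 scale with assumed values. The actual composite is rank-based, so its inflation may differ.

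**Counts (Results).** 44 - 40 = 4, and 4/44 = 9.1%. The single loss linked to the game is 1/44 = 2.3%. With blocks of 4, 44 is 11 full blocks, so allocation was 22:22 if every block was filled. The sequence split of the 40 completers is not in the text.

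**Formulas.** Let tau be the VR effect, pi the shift from first to second visit, s the SD of within-person differences within a sequence, a the number of completers with VR first, b the number with control first, and N = a + b.

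- The VR-minus-control difference has mean tau - pi with VR first, and tau + pi with control first.
- Mean of the unadjusted difference = tau + pi(b - a)/N.
- Expected SD² of the pooled differences = s² + pi²[1 - ((b - a)/N)²] × N/(N - 1).

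**Equal sequences (20:20), s = 2.5 assumed.** There is no bias.

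| Shift (points) | SD of difference | Variance ratio |
|---|---|---|
| 0 | 2.50 | 1.00 |
| 1 | sqrt(6.25 + 1 × 40/39) = 2.70 | 1.16 |
| 1.5 | sqrt(6.25 + 2.25 × 40/39) = 2.93 | 1.37 |
| 2 | sqrt(6.25 + 4 × 40/39) = 3.22 | 1.66 |

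Over s = 3 down to s = 2, the variance inflation is 11% to 26% for a 1-point shift and 46% to 103% for 2 points. The required size of a later crossover scales with this variance.

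**Error rates.** These come from 40,000 simulated trials per setting, with s = 2.5 and one-sided alpha 0.05 (assumed, as the article states none). At 20:20, type I error of the paired t test falls to 0.040 (1-point shift) or 0.018 (2 points). Power for a 1-point effect is 0.76 or 0.64, against 0.80 with period adjustment.

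**Unequal sequences, worst case.** If all four losses came from one sequence of a 22:22 allocation, the split is 22:18 and the bias is pi × 4/40 = 0.10 × pi: 0.10 points for a 1-point shift, 0.15 for 1.5 and 0.20 for 2. With a 1-point shift, type I error is 0.065 or 0.022, depending on direction, against about 0.05 adjusted.

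**What the four participants add.** A period-adjusted crossover model was evaluated with an assumed total SD of 2.5 per visit and the four losses split 2:2. Adding the four first visits changes the SE as follows:

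- correlation 0.3: 0.468 to 0.460 (1.7%)
- correlation 0.5: 0.395 to 0.390 (1.2%)
- correlation 0.7: 0.306 to 0.304 (0.8%)

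The 22:18 case gives gains in the same 1-2% range.

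**The case against.** **Intention-to-treat.** A reader might infer that a pairs-only analysis breaks the stated principle. The text does not support that. The principle is defined as analysis by assigned group, and neither Data Analysis nor the Abstract promises that every randomised participant enters every test. Analysis sets and missing-visit rules may also stand in a fuller document that is not shown. What remains is a tension, sharpest for the one participant who left over the game.

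**Period is already modelled.** A reader might also infer that the plan never adjusts for period, or does so only to study effect modification. Neither is right. The mixed models include period, fall back to a version without interactions, and can use one-visit data. That objection stands. However, those models are not the primary analysis. As listed, they also adjust for procedural anxiety, which VR is meant to change, and for the guardian anxiety inventory, which is collected only for participants under 18 in a sample reaching age 21. They are therefore not a clean source for the headline estimate.

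**Size.** The 9.1% figure can mislead. Three of the four losses were clinical, which Feasibility Outcomes separates from VR-related loss, and the gain in SE is slight. The shifts and SDs are assumptions on a scale other than that of the composite. The Discussion says that the pain stimulus is the same at each procedure, and a new series need not be a first laser exposure. These are fair limits, though an equal stimulus does not guarantee an equal response at a second visit. Even the worst-case bias for a 1.5-point shift, 0.15, is about a tenth of the smallest important difference quoted in Sample Size (1.4 points).

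**Choice between t and signed-rank.** The article bases this on the distribution of the scores, where the differences are what matter. Because the same paragraph also plans the SD of the difference, this may be only condensed wording.

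**Timing.** Data collection has ended and analysis is in progress, so this is a late change and must be documented as one.

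**Conclusion.** The point holds as a matter of precision and variance estimation. The primary test omits a period term that is standard for a two-period crossover and that the plan already uses elsewhere. With balanced sequences the paired estimate is unbiased, but its CI is too wide and the SD carried forward is too large: about 2.7 rather than 2.5 for a 1-point shift and 2.9 for 1.5 points, if the within-sequence SD is 2.5 NRS points. With no period shift, nothing is lost. Bias needs both a shift and unequal completers by sequence, and is at most 0.10 times the shift under a 22:22 allocation. The documents do not support a claim of serious bias, of a broken intention-to-treat rule, or of material information lost with the four participants. The true size on the composite cannot be known from the article. The change is worth making because it is cheap and because variance estimates are a stated purpose of the pilot.

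**What to change.** Before the biostatistician is unblinded, and with a dated record of the change and its reason:

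1. Make the primary aim 1 estimate period-adjusted: a random-intercept model on the composite score with treatment and period only, all 44 participants and every observed visit, reported with a 95% CI. It can be fitted with the treatments still labelled A and B.
2. If the within-person differences are clearly non-normal, compare the first-minus-second-visit differences between sequences by the rank-sum test. Half the Hodges-Lehmann shift is then the treatment effect. This option uses the 40 completers, and the report should say so.
3. For future sample sizing, report the period-adjusted residual SD. The SD of a within-person difference is sqrt(2) times that residual SD.
4. Keep the unadjusted paired t or signed-rank test on the 40 completers as a sensitivity analysis, named as such, and give the completers' split by sequence.

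The cost is one degree of freedom and a documented late change of primary analysis. No new data are needed, and the model is a reduced form of one already planned.

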**Methods:**

A total of 40 patients requiring outpatient laser therapy for at least 2 sessions will be recruited from a pediatric hospital in the Midwestern United States for this crossover randomized, 2-arm clinical trial. During the first laser visit, the participants will be randomly assigned to either play the VR-PAT game during their procedure or wear the headset with a dark screen. Participants will answer questions about their pain (Numeric Rating Scale 0‐10), anxiety (State-Trait Anxiety Inventory for Children, Numeric Rating Scale 0‐10, and Modified Yale Preoperative Anxiety Scale), and pain medication usage. Those playing the VR-PAT will report simulator sickness symptoms and their experience playing the game. At their second laser visit, participants will cross over to the opposite intervention. The primary outcomes are the differences in self-reported pain and anxiety between the 2 interventions. Feasibility outcomes include the proportion of screened patients who were eligible, have given consent, and completed both visits, as well as adverse events reported. To evaluate the efficacy of pain reduction, composite pain scores, and pain medication usage will be calculated for each laser visit. To evaluate the efficacy of anxiety reduction, the change in Modified Yale Preoperative Anxiety Scale scores will be compared between control and VR groups at each visit using the Wilcoxon rank sum tests. All statistical analyses will follow the intention-to-treat principle with regard to intervention assignment at each visit.

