## Methods

### Trial Design

We will conduct a prospective, 2-group crossover RCT with a 1:1 allocation ratio to either the intervention (VR-PAT gameplay) or the control (VR headset turned off) for the first laser appointment. Participants will crossover to the opposite group at their second laser appointment. Pain, anxiety, and VR engagement (for those in the intervention group) will be assessed after each research appointment, spaced approximately 6 to 8 weeks apart. The findings will be reported based on the CONSORT (Consolidated Standards of Reporting Trials) guidelines. This protocol is reported in accordance with the SPIRIT (Standard Protocol Items: Recommendations for Interventional Trials) guidelines (Checklist 1).

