### Sample Size

Since this is a pilot study, the focus of the statistical analysis will be on estimating the effect sizes of VR-PAT and their 95% CI, as well as the variances of the outcome measures. These findings will facilitate sample size calculations and study power estimates for future larger-scale randomized trials. We decided on a sample of 40 participants and 2 research visits based on the grant budget and the patient volume for the 1 dermatologist collaborating on this study.

Across acute pain studies, clinically meaningful improvements are generally larger than a 1-point change on the NRS 0‐10, with systematic review evidence suggesting minimum clinically important differences of approximately 13% to 36% reduction, with a median of 23% (IQR 18%-36%), corresponding to roughly 1.4‐2.3 points on the NRS [38,39].

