For aim 2, the mYPAS score had 6 repeated measurements over time (T0, T1, and T2 during each of the 2 laser procedures). At the first procedure, we will compare the change in mYPAS scores from T0 to T1 and T0 to T2 between the control and VR groups using either 2-sample 1-tailed *t* tests or the Wilcoxon rank sum tests (depending on the distribution of the change in mYPAS scores). The clinical effect size will be the difference in medians of the change in mYPAS, with the confidence limits calculated by bootstrapping with replacement using 1000 repetitions. Bootstrapping has been found to provide better confidence limits with asymmetric data, such as the mYPAS score in our study, and is the recommended method. The same statistical analysis approach has been successfully used by other researchers, who reported that VR effectively reduced preoperative anxiety among 71 children aged 5 to 12 years scheduled for elective surgery [42]. At the second procedure, we will compare the mYPAS scores at T0 and T1 between the control and VR groups using the Wilcoxon rank sum tests since mYPAS scores are shown to be asymmetric [42]. The clinical effect size will be the difference in medians of mYPAS. Confidence limits will be calculated using bootstrapping again.

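### The primary paired pain test, and with it the reported effect measure, is chosen from the per-visit composite scores instead of the within-participant differences

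*Protocol article*

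**What the plan says.** The Data Analysis section of the protocol article builds one composite score per laser procedure from pain and medication use, by a rank-based method taken from a cited source. VR and control procedures are then compared by a one-tailed paired t test or the Wilcoxon signed rank test, the choice being made "depending on the distribution of the composite scores) due to the cross-over design". The effect measure follows the test: a mean difference with the t test, or a "median difference (if Wilcoxon signed rank tests are used) in the composite score between VR and control procedures". The SD of the difference is reported in either case.

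The same section words its other rules differently. For the first-visit anxiety comparison (mYPAS), the choice is made "depending on the distribution of the change in mYPAS scores", which is the quantity being tested. The composite-score wording returns for the two-sample fallback on first-visit data, where it fits.

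The Sample Size section says that "the focus of the statistical analysis will be on estimating the effect sizes of VR-PAT and their 95% CI", together with the variances of the outcome measures.

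**The concern.** A paired t test needs roughly normal within-participant differences, and the signed rank test needs roughly symmetric ones. The shape of the visit-level scores governs neither. A score built from ranks and medication use is likely to look flat or lumpy, so a check on the scores can fail when the differences give no reason to abandon the t test.

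The same check also decides what is estimated. This is a pilot whose stated product is an effect size with a confidence interval, meant to inform a larger trial. A diagnostic on the wrong variable should not decide whether that effect is a mean or a median. The SD of the difference, which is reported either way, belongs with a mean and not with a median.

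The term median difference is also left open. It could be the median of the paired differences, the difference between the two visit medians, or the Hodges-Lehmann estimate, and these differ in precision.

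**Working it through.** **Inputs from the documents.** The design is a "2-group crossover RCT with a 1:1 allocation ratio". The sample was set by resources: "We decided on a sample of 40 participants and 2 research visits based on the grant budget" and on patient volume. "A total of 44 patients were recruited and completed the first visit, with 40 participants completing both visits", so 44 - 4 = 40 pairs. The article gives no alpha, power or planning SD, so there is no sample size figure to reproduce. It also gives no composite formula and no normality criterion, so these are assumed below.

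**Step 1: which quantity matters.** Write the composite of participant i at visit v as C_iv = a_i + (VR or control effect) + e_iv, where a_i is the participant's own level. Let d_i = C_i,VR - C_i,control.
- Paired t test: t = mean(d) / (SD(d)/√40).
- Signed rank test: the sum of the ranks of |d_i| over the pairs with d_i > 0.
- Hodges-Lehmann estimate: the median of all (d_i + d_j)/2 with i ≤ j.

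All three use only the d_i. The term a_i cancels, so a lumpy spread of participant levels (for example, some participants medicated at both visits) shapes the scores and leaves the differences untouched.

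**Step 2: how often the two checks part.** Simulations of 40 pairs used a composite made of summed ranks of pain and medication, and Shapiro-Wilk at 0.05 as the check. All of this is assumed. SE ratios are relative to the mean difference.

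| Assumptions | Scores fail | Differences fail | SE ratio, median of differences | SE ratio, Hodges-Lehmann |
|---|---|---|---|---|
| A: whole-number pain, SD 2.5, 1-point effect, correlation 0.3-0.7, medication at 0-50% of visits | 60-100% | 4-13% | 1.15-1.35 | up to about 1.06 |
| B: pain rounded and clipped to 0-10, symmetric or skewed; 1-point shift; correlation 0.3, 0.5, 0.7; medication 0, 15, 30, 50% (2 × 3 × 4 = 24 settings) | 99-100% (80 scores pooled); 89-100% (either visit's 40) | 4-32% | 0.98-1.39 | 0.91-1.06 |
| C: another sum-of-ranks run | 62-100% | 3-13% | 1.12-1.39 | 1.00-1.07 |

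Under B, the scores fail while the differences pass in 68-95% of runs.

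**Step 3: what the switch costs in precision.** Under B, the result depends on what drives the differences.
- Pain alone varies (no medication, or the same use at both visits): ratio 1.25-1.39. Example, skewed pain, correlation 0.3, no medication: 14.47 / 10.39 = 1.39. In variance terms 1.39² = 1.93, so 40 pairs analysed by the median inform about as much as 40 / 1.93 ≈ 21 pairs analysed by the mean.
- Medication use varies between visits: ratio 0.98-1.11, with several settings within simulation error of 1. Example, skewed pain, correlation 0.7, 30% medication: 11.78 / 11.99 = 0.98.
- Difference between the two visit medians: ratio 1.5-2.3.

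**Step 4: what it costs in power.** At an assumed one-tailed alpha of 0.05, power of the t test minus power of the signed rank test lies between about -4 and +2 percentage points.

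**The case against.** The strongest reply is that the size of the problem rests on inputs the article does not give. The composite formula sits in a cited source, no formal normality test is named, and an article may leave the diagnostic to the analysis plan. If the median difference is meant as the Hodges-Lehmann estimate, the loss of precision disappears. The mixed-effects models in the same section put a VR effect on the mean scale whichever paired test is used, and they are said to supply planning data for the next trial. The biostatistician works with masked group labels for the primary outcome, which limits any steering of the choice. Choosing between a t test and a Wilcoxon test is also common in pilots.

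Most of this stands as a limit on size. It does not rescue the rule, because the article states the quantity to be checked, and states the wrong one. That is different from leaving a detail out.

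Three stronger readings are tempting and are not supported:
- *The plan will yield a clearly noisier estimate.* This holds only under some assumptions. Where medication use varies between visits, set B shows little or no loss.
- *The primary test is compromised.* Power is nearly the same on both branches.
- *The anxiety analysis has the same fault.* Its first-visit rule is keyed to the change, and its effect measure is fixed as a difference in medians with bootstrap limits. The abstract names only the rank sum test, "at each visit using the Wilcoxon rank sum tests", while Data Analysis also allows a t test at the first procedure. That is a separate, minor wording mismatch.

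**Conclusion.** The point holds as a wrongly stated rule in the primary pain analysis: the check belongs on the within-participant differences, and the reported effect measure should not depend on it. All three sets of assumptions agree that the scores fail a normality check far more often than the differences do. The percentages belong to the assumed composite and check, and would change with the cited formula or an informal look at plots.

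The harm falls on the estimate and its confidence interval, not on the test. It ranges from nothing to a standard error about 39% larger for the plain median of paired differences, and is small for Hodges-Lehmann. It would be largest (1.5-2.3 times) if the difference between visit medians were reported. With the mean-scale estimate also available from the mixed models, this is a wording correction worth making before the analysis is run. It is not a flaw that invalidates the trial.

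**What to change.** Before the primary analysis is run, and before group labels are disclosed to the biostatistician:
- Prespecify one paired effect measure with its 95% CI, for example the mean within-participant difference in composite score.
- Give the signed rank test with the Hodges-Lehmann estimate and its CI as sensitivity analysis, and say that this is what is meant by a median difference.
- Delete the choice based on the composite scores. If a distribution check is kept, apply it to the within-participant differences and state that it does not change the reported effect measure.
- Separately, name one test for the first-visit mYPAS change so that the abstract and Data Analysis agree.

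The cost is wording only. What is lost is the option to switch method after seeing the data. The abstract describes data analysis as already in progress, so the change should be dated. If the paired comparison has already been run, both effect measures should be reported.

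### The clinical effect size for pain is defined only on a rank-based composite, while the protocol's benchmark and its listed primary pain outcomes are in NRS points and no conversion is given

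*Protocol article*

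**What the plan says.** Under Data Analysis, aim 1 rests on a composite for each procedure, "encompassing the pain score, pain medication use during the procedure, and whether rescue medication was used". On its construction the article says "we will apply the rank-based approach" of a cited source, "to assign weights to pain and medication use, reflecting their complementary clinical importance as measures of pain reduction". The formula is not shown. The VR and control visits are compared on this composite with a paired t test or a Wilcoxon signed rank test. The effect measure follows: "The clinical effect size will be the mean difference (if paired" t tests are used, otherwise the median difference, in either case "in the composite score between VR and control procedures. The SD of the difference will also be calculated". The mixed models later in the same section are also fitted to the composite, and their results are meant to inform the size and power of a future study.

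Under Sample Size, the pilot is to estimate effect sizes with 95% CIs and the variances of the outcome measures: "These findings will facilitate sample size calculations and study power estimates for future larger-scale randomized trials". Clinical relevance is stated there on one scale only: "clinically meaningful improvements are generally larger than a 1-point change on the NRS" from 0 to 10, with a range of roughly 1.4 to 2.3 points.

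Primary Outcomes does not list the composite for pain. It lists three self-ratings on the 0 to 10 NRS (worst pain, average pain and time thinking about pain), to be compared between VR and control visits.

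**The concern.** The quantity called the clinical effect size and the standard for judging clinical importance are on different scales, and nothing links them. A composite of pain and medication use is not in NRS points, whatever its exact formula. The article gives neither a meaningful difference on the composite nor a conversion. A composite difference can also move for reasons other than a change in pain points: a different spread of pain in the sample, or a different mix of medication use at the two kinds of visit.

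Two uses are at stake. The first is reading the result: a composite difference alone does not say whether 1.4 to 2.3 points was reached. The second is planning: a later trial with an NRS endpoint needs a difference and an SD in points, and the composite does not supply them. For aim 2 the same section states the effect size in the native units of the anxiety scale, so the mismatch is specific to pain.

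**Working it through.** **No figure to reproduce.** The 40 participants are justified by budget and patient volume. No SD, target difference or power is stated. The check is therefore whether a composite difference can be read as NRS points, and what can be carried forward from it.

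**Assumptions (none is given in the protocol).** 40 pairs; NRS scores rounded and limited to 0–10; control mean 5; within-person correlation 0.5; true reduction 1.4 points before rounding and truncation; a yes/no medication indicator. Pain and medication were each ranked over all 80 visits, and the composite was the sum of the two ranks. Rescue use was not modelled separately. Each setting was simulated 600 times, and results vary by a few tenths between runs. Differences are control minus VR, so positive values favour VR.

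**Step 1: composite difference against NRS difference.**

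| NRS SD | Medication use, control/VR | NRS difference | Composite difference | SD of composite difference | Ratio |
|---|---|---|---|---|---|
| 1.5 | 30/30% | 1.39 | 18.9 | 30.2 | 0.62 |
| 2.0 | 30/30% | 1.37 | 15.2 | 30.9 | 0.49 |
| 2.5 | 30/30% | 1.30 | 12.1 | 31.3 | 0.39 |
| 3.0 | 30/30% | 1.24 | 10.4 | 31.4 | 0.33 |
| 2.5 | none | 1.30 | 12.1 | 23.0 | 0.53 |
| 2.5 | 50/50% | 1.29 | 11.8 | 32.2 | 0.37 |
| 2.5 | 50/30% | 1.33 | 20.1 | 31.9 | 0.63 |
| 2.5 | 30/50% | 1.32 | 4.1 | 32.0 | 0.13 |
| 2.5 | 60/30%, no pain shift | 0.0 | 11.9 | 32.6 | 0.37 |

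Roughly the same pain reduction in points gives composite differences from 4.1 to 20.1. A difference of about 12 arises both from a true 1.4-point shift and from no pain shift at all. A second assumed scoring, the percentage deviation from the mean rank, showed the same pattern.

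**Step 2: what can be carried forward.** With NRS SD 2.5 and 30/30% medication use, the raw rank-sum difference and its SD grow with the pilot's size:

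| Pairs | Difference | SD of difference | Ratio |
|---|---|---|---|
| 20 | 6.2 | 15.4 | 0.40 |
| 40 | 12.5 | 31.3 | 0.40 |
| 100 | 30.0 | 78.3 | 0.38 |
| 200 | 60.6 | 156.1 | 0.39 |

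The raw values depend on the pilot's size; the ratio does not. For a paired trial at two-sided 0.05 and 80% power, N = ((1.96 + 0.84) × SD / difference)². With unrounded inputs:

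- Composite, matched values from 40 pairs (12.45 and 31.25): 50 pairs.
- Composite, difference from 40 pairs with SD from 100 pairs (78.25): 311 pairs, which is wrong.
- NRS, same scenario (1.33 and 2.42): 26 pairs.

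The composite ratio sizes a trial on the composite; it does not give the size of a trial on the NRS.

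**Step 3: what the NRS estimate would offer.** With 40 pairs the 95% half-width is t(0.975; 39 df) × SD / √40. For an assumed SD of the difference of 2, 2.5 or 3 points this is 0.64, 0.80 or 0.96 points. An observed 1.4 with SD 2.5 would have the interval 0.6 to 2.2, which can be set directly against 1.4 to 2.3.

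**The case against.** **NRS results are already in the plan.** Primary Outcomes promises a comparison of the NRS items between visits, and Sample Size promises variances of the outcome measures. This stands. A reader might infer that the trial cannot say whether the important difference is reached. The documents do not support that: NRS results are not excluded. What remains is that the only pain effect size actually defined is on the composite. That is a stated choice of measure, not a detail left to a fuller document.

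**The composite can size a later trial.** This also stands. A reader might infer that nothing can be carried forward, but the mean difference over the SD of the difference is unit-free and stable across pilot sizes. The limits are a different endpoint, a different medication mix (the ratio ran from 0.13 to 0.63) and a parallel-group design, which also needs the between-person SD. If the Wilcoxon branch is taken, a median difference paired with an SD is not a proper standardised effect.

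**Ranking does not fix the spread the plan reports.** The SD of 80 untied ranks is √((80² − 1)/12) = 23.1 whatever the pain variability. It is tempting to conclude that the reported SD carries no information. The plan reports the SD of the paired difference, however. With pain ranks alone and no effect, that SD was 29.5, 23.8 and 15.7 at within-person correlations of 0.2, 0.5 and 0.8. It does carry the within-person information that a paired trial needs.

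**The benchmark is not shown to be inconsistent.** Pairing 13% with 1.4 points would imply a baseline of 1.4/0.13 = 10.8, off the scale. The article does not make that pairing. Pairing the median of 23% with 1.4 and 36% with 2.3 gives 6.1 and 6.4, which is coherent.

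**No decision depends on it.** The scale-up thresholds under Feasibility Outcomes are serious adverse events, loss due to VR, and satisfaction. This limits the consequence to interpretation and planning.

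**Conclusion.** The point holds in limited form. The clinical effect size for pain is defined on a composite with no benchmark and no conversion, while clinical relevance and the listed primary pain outcomes are in NRS points. On its own it cannot show whether roughly 1.4 to 2.3 points was reached, and it cannot size a later trial with an NRS endpoint. It can, as a ratio to the SD of the difference, size a paired trial on the same composite in a similar population with similar medication use.

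The mismatch of scales follows from the text alone. The figures (composite differences of 4.1 to 20.1 for about the same pain shift; 50 against 26 pairs) are illustrations. They rest on an assumed scoring, because the composite formula is in a source not shown, and on assumed pain and medication distributions. That the units come from the ranking is a reasonable inference from the description, not a stated fact. The change is worth making before the results are reported, but the gap does not invalidate the planned test.

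**What to change.** In Data Analysis, keep the composite for the planned test but no longer call its difference the clinical effect size. Name instead the paired VR-minus-control difference in NRS points for the listed pain items, with its 95% CI and the SD of the difference. State that this is the estimate to be read against the benchmark under Sample Size and used for planning. Show a summary of medication use by visit type beside it. Report the composite effect in standardised form, as mean difference divided by SD of the difference, whichever test is used.

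The cost is a wording change and one more set of estimates. Results states that data collection is complete and analysis is still under way, so the scores are in hand. The change should be dated and made before the treatment labels are revealed to the biostatistician. The downside is that the NRS estimate does not account for medication use: a pain difference could be masked or exaggerated if use differs between visits. The medication summary is therefore a necessary companion to it.
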